### Selection of study participants

#### Recruitment

Pregnant women in the first or second trimester of their pregnancy, living in the Taabo HDSS with an age ≥ 15 and ≤ 49 years will be eligible to participate in this study. Gestational length will be assessed based on self-reported date of conception or date of last menstrual period. Key informants will be recruited by the study team in all areas to report pregnancies as early as possible to the study staff. Key informants will be given a reward of 1000 CFA (approximately USD 2) for each pregnancy reported. Once the study coordinator has been informed about a new pregnancy, a local field enumerator will be sent out to invite pregnant women to participate in the study. Conditional on her consent, the women will be automatically assigned to a group based on her residence and a short baseline questionnaire will be conducted.

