### Intervention

As part of this study, we will test two interventions: an information only intervention and an information plus delivery intervention.

The information only intervention focuses on empowering pregnant mothers to adopt appropriate health practices and health behaviour. Health staff (midwives and nurses) will visit all women in this arm at the beginning of their pregnancy (after baseline) and inform women regarding the importance of antenatal IFAS as well as IPTp. Specifically, the nurse will talk with participating women about the benefits, adverse events, and when, why, and how to take IFAS and sulfadoxine-pyrimethamine (SP). The nurse will also provide pregnant women with a phone number they can call in case they have questions related to antenatal care, supplements or IPTp, and will encourage women to attend antenatal care in accordance with national guidelines.

In the information plus delivery arm, women will receive a similar first visit by a study nurse, followed by monthly home visits. During the initial visit, study staff will inform women about recommended antenatal care attendance and supplementation and inquire about supplements received. All women not having received supplements from their antenatal care visits will be then be directly provided with a monthly supply of iron and folic acid. Similarly, all women in their second or third trimester not having received SP will be directly provided SP together with additional information and instructions on how to take the medication each month. At the end of each monthly visit, study staff will remind women about their next antenatal care appointment and remind them to take supplements daily.

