### Data collection

Table 1 presents a summary of all measurements conducted in the study. Data will be collected by a trained researcher team. In addition to the baseline collection, we will collect detailed monitoring data on home visits as well as cost data for the two arms. To assess the relative effectiveness of each strategy, we will conduct an endline survey within the first 2 weeks after delivery. The form to be used to conduct the endline survey among women will combine both information on prenatal supplementation and IPTp (supplements, doses, period, frequency, and date, anaemia and malaria status), socio-demographic characteristics e.g. (maternal age, education attainment and household assets), and pregnancy outcome (e.g. live birth, still birth, preterm birth and birth weight,). Given that we expect women’s self-report on antenatal IFAS not be very accurate, we will collect haemoglobin level and malaria infection prevalence as primary study outcome measures at endline. Haemoglobin levels will be assessed using HEMOCUE devices; malaria infection will be tested using standard rapid diagnostic tests (RDTs). All endline surveys will be conducted by study nurses who are familiar with both test procedures.

**Table 1 Tab1:** Overview of study outcomes and measurements

	Baseline	Endline (6 months)

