**Pregnancy related information after delivery**		
Pregnancy outcome		X
Child’s sex		X
Birth weight		X
Place of delivery		X
Assistance during delivery		X
Delivery process		X
Delivery cost		X
Performed tests during ANC		X
Antenatal IFAS uptake (number, dose)		X
Malaria prevention (number, dose)		X
Adverse events from iron uptake		X
Haemoglobin level		X
Malaria infection		X

*ANC* antenatal care; *IFAS* iron and folic acid supplements

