### Sample determination

The unit of randomization will be neighborhoods, locally referred to as “quartiers” or “hamlets”. The study is powered to detect a 20%pt. decline in maternal anaemia with power 0.8 and alpha 0.05, assuming a control group anaemia prevalence of 50%, 6 women per cluster, and an intra-class correlation (ICC) of 0.25. The ICC estimate was based on a previous analysis of antenatal care access patterns in the Taabo HDSS. Assuming a follow-up rate of 90%, this requires an initial enrolment of 240 women per arm, or a sample of 720 women in total. Given the births rates observed in the past 3 years, we anticipate to enroll these 720 women over a 6-month period. Based on the latest Demographic and Health Survey conducted in the region, we expect 21% of women in the control group to be malaria positive. In order to achieve power 0.8, we would need a two third reduction in RDT positivity after birth with the intervention.

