### Statistical analyses

The health outcomes to be studied are post-partum anaemia, malaria infection, and birth weight. Post-partum anaemia will be defined as a haemoglobin concentration less than 11 g/dL and malaria infection will be defined by a positive result of the RDT. Logistic regression models will be used to compare post-partum anaemia and malaria infection in the two intervention groups to the control group. For birth weight as well as haemoglobin levels as continuous variable, we will use basic linear regression models. Generalized estimating equations with robust variance-covariance estimation will be used to account for clustering [27, 28]. The basic regressions models will compare outcomes in treated and control women, with standard error corrections for grouped data. In adjusted estimates, we will control for basic maternal covariates such as age, education, and residence. The power calculations were done as two-group comparisons, allowing to estimate differences between either of the two intervention groups and the control group. Additional subgroup analysis focusing only on a dose-response analysis will also be conducted to estimate average treatment effects on the treated.

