### Access to care during and after the trial and compensation

All subjects will have access to public antenatal and post-natal care during and after the trial. Women in both treatment and control groups with diagnosed malaria infections and haemoglobin levels below 11 g/dl will be referred to the nearest health centre for further testing and treatment. No compensation will be provided to study subjects.

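### The planned dose-response analysis gives an association, not the average treatment effect on the treated that the protocol attaches to it

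*Protocol article*

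**What the plan says.** The Statistical analyses section of the protocol article first compares each intervention group with control, by logistic or linear models with generalised estimating equations and robust variances. Adjusted estimates use maternal covariates, with age, education and residence given as examples. The section then adds one sentence: "Additional subgroup analysis focusing only on a dose-response analysis will also be conducted to estimate average treatment effects on the treated". It does not define dose, and it mentions no instrument, intake model or use of the random assignment for this analysis.

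Other sections bear on what dose can mean:

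- **Sample determination:** the units randomised are neighbourhoods and hamlets.
- **Table 1:** among the measurements after delivery is "Antenatal IFAS uptake (number, dose"; malaria prevention is listed in the same form. Both are recorded at endline.
- **Data collection:** haemoglobin and malaria tests were chosen as primary outcome measures for this reason: "Given that we expect women’s self-report on antenatal IFAS not be very accurate".
- **Intervention:** in the delivery arm, "All women not having received supplements from their antenatal care visits will be then be directly provided with a monthly supply". Visits are monthly.
- **Recruitment:** those eligible are "Pregnant women in the first or second trimester of their pregnancy".
- **Access to care:** "All subjects will have access to public antenatal and post-natal care during and after the trial". The Discussion puts local iron and folic acid coverage below one half, so it is not zero.

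**The concern.** The sentence pairs a method with a causal quantity that the method does not deliver. An effect on the treated needs a comparison in which, apart from treatment, the treated and their comparators would have had the same outcomes. Randomisation provides that between arms. It does not provide it between women who took more and women who took less, because intake was the women's own doing or was decided by rules that depend on their behaviour and their pregnancy.

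The result would come from a randomised trial and carry a causal label, so readers would give it the trial's authority. It could suggest benefit where supplements do nothing, or exaggerate a real benefit. Birth weight is the most exposed outcome: a short pregnancy lowers both the number of monthly visits and the weight of the child.

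**Working it through.** **1. Sample available.** The documents give no figure for this analysis, so the only figure to reproduce is the sample size.

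- Anaemia 50% vs 30%, two-sided 5%, power 0.80, pooled formula: [1.960 × √(2 × 0.4 × 0.6) + 0.842 × √(0.25 + 0.21)]² / 0.20² = 93 per arm.
- Design effect 1 + (6 − 1) × 0.25 = 2.25, and 93 × 2.25 = 209.25, taken as 210.
- 210 / 0.9 = 234, against the stated 240 (within 3%).
- Followed up per arm: 240 × 0.9 = 216. Delivery plus control: 432.

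**2. Does any reading of dose give the stated estimand?**

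| Reading | What determines it | What the slope estimates |
|---|---|---|
| Uptake reported at endline (natural reading, Table 1) | Care-seeking, side effects, gestation at entry, reporting error | Confounded association |
| Supplements delivered by the study | Not having obtained them at antenatal care | Association selected by design |
| Cumulative count of visits or supplies | Gestation at entry and at delivery | Association tied to length of pregnancy |
| Arm as an ordered dose | Randomisation | Intention-to-treat trend, not an effect on the treated |

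**3. Spurious significance under no effect (assumed model).** Let U be unmeasured care-seeking and A the arm (0/1). Dose = bU + 0.6A + noise and outcome = bU + noise, with unit variances within arm. Neither arm nor dose affects the outcome. Then:

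- corr(dose, outcome) = b² / √(1 + 0.6² × 0.25) = b² / 1.044
- expected z ≈ √432 × b² / 1.044 = 19.9 b²
- rejection rate = Φ(z − 1.96) + Φ(−z − 1.96)

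| b | z | Rejection, formula | Simulated, no clustering | Simulated, ICC 0.25, cluster-robust errors |
|---|---|---|---|---|
| 0.1 | 0.20 | 5% | – | about 6% |
| 0.2 | 0.80 | 13% | 12–14% | 10% |
| 0.3 | 1.79 | 43% | 43–46% | 34% |
| 0.4 | 3.19 | 89% | 88–90% | 81% |

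The comparison by randomised arm stays at 4–6%. The values of b and the 0.6 are assumptions.

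**4. Size on the anaemia scale (assumed model).** Intake is 45% in control and 75% in the delivery arm, with 216 followed up per arm. Clustering is ignored because only bias is examined. U shifts both intake and anaemia.

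| Confounding | Takers minus non-takers, true effect 0 | Takers minus non-takers, true effect −20 points |
|---|---|---|
| None | 0 | −20 |
| Weak | −3 | −23 |
| Moderate | −8 | −28 |
| Strong | −15 | −35 |

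The difference between arms divided by the difference in intake stays within about 1 point of 0 and at −19 to −21 points respectively. In this model, however, arm acts only through intake by construction, which the trial cannot guarantee.

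**5. Birth weight and visit count alone.** Assume no confounder and no effect of visits, delivery at 39 ± 2 weeks, entry uniform over 8–26 weeks, and 130 g per week of gestation.

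- Visits ≈ (delivery − entry) / 4, so the variance is (2² + 18²/12) / 16 = 31/16 = 1.94.
- Covariance with birth weight = 130 × 2² / 4 = 130.
- Slope = 130 / 1.94 = 67 g per visit before rounding to whole visits.

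Simulation gave about 62 g per visit, significant in 71% of trials. The 71% also depends on the residual scatter assumed for birth weight.

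**The case against.** The sentence defines neither dose nor estimator, and this is a condensed article. A reader might infer that the protocol commits to an analysis by supplements actually taken, or by cumulative dose. It does not say either. Reported uptake is the natural reading because it is the dose variable that Table 1 lists, but it remains an inference. A dose per month of exposure would weaken the mechanical link with preterm birth. A fuller plan could also use assignment as an instrument. The covariate list is open-ended, and Table 1 records pregnancy duration and antenatal attendance at baseline.

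All of that stands as a limit on how firmly one can say what will be done. It does not rescue the pairing. None of the four readings above identifies an effect on the treated by a dose-response slope, and adjustment for baseline variables leaves later care-seeking, side effects and length of pregnancy untouched. An instrument would also not deliver the stated quantity: control women can obtain the same products, so it gives a complier effect.

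It is also fair that the simulated rates rest on invented inputs. At b = 0.1 there is almost no inflation, and clustering lowers the rates at higher b. No single rate should be quoted as the size of the problem.

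Finally, the analysis is additional. The comparisons by arm, the sample size and the cost-effectiveness ratio do not depend on it.

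**Conclusion.** The method and the estimand do not match. The slope is an association and should not be reported as an average treatment effect on the treated. This rests on the protocol's own text: cluster randomisation, supplementation conditional on antenatal receipt, open access to public care, and variable gestation at entry.

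The size of the bias cannot be had from the documents. Under assumed confounding, the false-positive rate of the slope runs from about nominal to about 90%, and the spurious anaemia difference from 0 to 15 points, against a design target of 20.

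A reader might infer that the trial's main findings are compromised. The documents do not support that, because the primary comparisons follow randomisation. This is a point that should be fixed, not one that must be fixed before the trial can be interpreted.

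**What to change.** Replace the sentence with:

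> A dose-response analysis, with dose defined in advance, will be reported as exploratory and associational and will not be interpreted as an effect of treatment on the treated; birth weight will not be regressed on cumulative dose.

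This changes one sentence, needs no new data, and gives up only a causal claim that the analysis could not support.

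Optionally, if an effect of changed intake is wanted, add a sensitivity analysis with randomised arm (delivery vs control) as instrument and cluster-robust errors. Label it a complier effect of the bundled package and state its limits:

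- The exclusion restriction is doubtful, because the arm bundles information, reminders, iron and folic acid, and sulfadoxine-pyrimethamine (SP).
- One contrast between arms cannot separate the supplements from SP.
- Intake is self-reported, and the protocol itself expects the supplement reports to be inaccurate; reporting that differs by arm would distort the estimate.
- Intervals will be wider than for the comparison by arm.

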### Access to care during and after the trial and compensation

All subjects will have access to public antenatal and post-natal care during and after the trial. Women in both treatment and control groups with diagnosed malaria infections and haemoglobin levels below 11 g/dl will be referred to the nearest health centre for further testing and treatment. No compensation will be provided to study subjects.

### Cost and cost-effectiveness

Throughout the trial, detailed cost data for implementing both intervention arms will be collected. The data will be used to compare the observed increases in supplementation coverage to the cost of each arm. Incremental cost effectiveness ratios will be defined as additional cost per pregnant woman divided by the observed increase in the probability of receiving appropriate ANC (IPTp + IFAS).

## Discussion

This paper describes the design of a cluster-randomized study that will evaluate the effectiveness and cost-effectiveness of two alternative strategies in increasing IFAS and malaria chemoprophylaxis coverage among pregnant women relative to the current default system. To our knowledge, this is the first study in Côte d’Ivoire using data stem from an HDSS, which is a well-characterized population-based cohort that is subject to longitudinal surveillance. Results from this study will help in identifying the most effective and cost-effective strategy to increase antenatal IFAS and IPTp coverage in rural Côte d’Ivoire and similar settings. The results of the study will be shared through a peer-reviewed article as well as through the communication offices at the Centre Suisse de Recherches Scientifiques and the Swiss Tropical and Public Health Institute.

The choice of interventions is made not only based on the results of past studies [16–18] but also on the priority of national challenges in maternal and child health. The latest data from the Taabo HDSS suggests that prenatal supplementation with iron and folic acid covers less than 50% of pregnant women. IPTp has been adopted since 2005. However, the effectiveness of protecting the mothers and unborn child from adverse events from malaria depend on the rigorous adherence of this policy, coverage, and the number of ANC visits of the expectant mothers [29, 30].

The implementation of this project into the Taabo HDSS will make recruitment of the participants easy. The project will also be conducted in close collaboration between the Centre Suisse de Recherches Scientifiques, Swiss Tropical and Public Health Institute, local physicians and nurses, and communities leaders based on mutual agreement with local authorities from the whole HDSS’s area to guarantee smooth implementation. The Taabo HDSS platform reduces the risk for loss to follow-up since the fieldwork teams hold close contact with the local population.

Although the study is designed as a cluster-randomized controlled trial, contamination between hamlets or neighbourhoods cannot be excluded. In cases where clusters correspond to hamlets, the next settlement is typically at least 1 km away. For urban neighbourhoods, distances are much smaller, with households on the opposite side of the street receiving opposite treatments in some cases. For the direct delivery arm, spillovers seem somewhat unlikely, because the study team will simply not deliver the same intervention to non-treated women. For the information only treatment, spillovers are certainly possible, and would bias the estimated impacts towards zero. We will explore such contamination effects through spatial analysis in our sensitivity checks.

The project team may also face some push-back or complaints regarding adverse events related to iron consumption. We will make subjects aware of this risk in the informed consent form and use the initial information session to further prepare pregnant women for this. We will also try to minimize these adverse events by asking mothers who have complaints to take supplements after major meals. Another problem is that some women may not attend ANC if they receive supplements at home. ANC attendance is critical for preparing women for delivery, for understanding warming signs during pregnancy and childbirth, and for the prevention of pregnancy-related morbidity factors. To ensure attendance to ANC, all women will be reminded to attend the scheduled visits during the first visit in both arms, and during each of the visits by our study team in the home delivery arm.

Last, there are some concerns that folic acid supplementation may increase the rate of treatment failures with SP [31]. Given that national protocols demand both iron and folic acid supplements, we cannot investigate this question experimentally in our study – post-hoc analysis of relative SP efficacy among women taking and not taking iron and folic acid supplements may however be possible.

## Data Availability

The data collected as part of this trial will be made available to researchers upon publication of the main results.

## Abbreviations

IPTp: Intermittent preventive treatment of malaria in pregnancy
HDSS: Health and demographic surveillance system
LMICs: Low- and middle-income countries
SP: Sulfadoxine-pyrimethamine
